### Endpoints

2.5

The primary endpoint is the change in HbA1c from baseline to week 52. Secondary endpoints are changes in self-reported diabetes distress, quality of life, and treatment satisfaction. Primary, secondary, and exploratory endpoints are listed in **Table 3**.

**Table 3 T3:** Endpoints.

Primary endpoint
Change in HbA1c from baseline to week 52

Secondary endpoints
Changes in DDS (Diabetes Distress Scale) score from baseline to week 52 Change in ADDQoL (Audit of Diabetes Dependent Quality of Life) score from baseline to week 52 DTSQc (Diabetes Treatment Satisfaction Questionnaire) score at week 52

Exploratory endpoints
Changes in DTSQs score from baseline to week 52 Change in HCQ (Hypoglycemia Confidence Questionnaire) score from baseline to week 52 Proportion of patients with HbA1c 58 mmol/mol (7.5%) or less at 52 weeks Proportion of patients with HbA1c 52 mmol/mol (6.9) or less at 52 weeks Proportion of patients lowering HbA1c 5 mmol/mol (0.46) or more from baseline to week 52 Change in total insulin dose from baseline to week 52 Change in weight from baseline to week 52 Change in blood pressure from baseline to week 52

### Statistics

2.6

#### Sample size calculation

2.6.1

The study is powered to detect an improvement in HbA1c of 4.4 mmol/mol (0.4 percentage units) from baseline to week 52. We assumed an SD of 8.7 mmol/mol (0.8%) for change in HbA1c for both treatment groups (23), showing that 64 individuals per group are needed to obtain a 80% power at an alpha level of 0.05. Accounting for a drop-out rate of 10%, 142 individuals were needed.

#### Primary efficacy analysis

2.6.2

The primary efficacy analysis is the change in HbA1c from baseline to 52 weeks follow-up between the two groups using analysis of covariance (ANCOVA) with HbA1c at baseline as covariate in the ITT population, two-sided test of significance level 0.05.

#### Secondary efficacy analysis

2.6.3

The secondary efficacy analysis is the change in diabetes distress scale (DDS) score from baseline to week 52 in the two treatment groups using ANCOVA with DDS score at baseline as the covariate. In case the assumption of normal distribution is not met, an effort to transform data to normal distribution will be made. If the assumption of normal distribution is still not met after transformation of data, logistic regression will be used with grouping variable as the dependent variable, change in DDS as main effect variable, and DDS score at baseline as the covariate.

Change in the quality-of-life score from baseline to week 52 between the two treatment groups will be analyzed using the same methodology as for the DDS score.

DTSQc score at week 52 between the two treatment groups will be analyzed using ANCOVA in case the assumption of normal distribution is met, or otherwise by using the Mann-Whitney U-test.

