#### Exploratory analyses

2.6.4

Exploratory endpoints will be analyzed in the same way as the primary and secondary endpoints, using ANCOVA for normally distributed variables, ANCOVA on transformed variables in case the assumption of normal distribution is not met, or logistic regression as described above. All exploratory endpoints will be adjusted for baseline values. Possible differences may exist depending on the distribution of variables.

An exploratory analysis is planned describing the psychological methods used by psychologists in the study and an analyses with respect to if results differed by psychologist, i.e. if an interaction exist between psychologist and treatment effect. We will also analyze if treatment effects relate to the number of consultations with psychologist.

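### For DDS, ADDQoL and the continuous exploratory endpoints, the last-resort fallback models treatment arm from the change score, so it tests a difference but gives no effect size in score points

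*Protocol article*

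**What the plan says.** Section 2.6.3 (Secondary efficacy analysis) sets a three-step chain for change in DDS to week 52.

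1. Change is compared "in the two treatment groups using ANCOVA with DDS score at baseline as the covariate".
2. The second step is a transformation: "In case the assumption of normal distribution is not met, an effort to transform data to normal distribution will be made".
3. Should normality fail even then, the plan turns to a third model: "logistic regression will be used with grouping variable as the dependent variable, change in DDS as main effect variable", with baseline DDS as covariate.

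Change in quality of life (ADDQoL) "will be analyzed using the same methodology as for the DDS score". For the exploratory endpoints, section 2.6.4 lists ANCOVA, then "ANCOVA on transformed variables in case the assumption of normal distribution is not met, or logistic regression as described above". Table 3 shows which endpoints this covers. Five are changes in continuous measures: DTSQs, hypoglycemia confidence, insulin dose, weight and blood pressure. Three are HbA1c proportions, such as "Proportion of patients with HbA1c 58 mmol/mol (7.5%) or less at 52 weeks".

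Two analyses lie outside the chain. DTSQc is compared by ANCOVA, "otherwise by using the Mann-Whitney U-test". For the primary HbA1c analysis, section 2.6.2 states ANCOVA with no fallback.

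**The concern.** Arm is fixed by 1:1 randomization, and change in DDS is what treatment may alter. The fallback swaps these roles. Its coefficient answers how well the change score predicts the arm a patient was allocated to, not how many points treatment moves the score. The text names the dependent variable, the main effect and the covariate one by one, so this is a stated rule and not detail lost in condensing the protocol.

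At stake is the effect size for the distress and quality-of-life endpoints. The Discussion says that a psychosocial gain without a glucose effect would still matter to patients in practice. To judge such a gain, a reader needs a difference in score points with an interval, to compare with a meaningful change or to pool with other trials. If the fallback is triggered, the planned model does not supply one.

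**Working it through.** **Sample size used.** The article states 64 per group (section 2.6.1). With n = 2(1.96 + 0.84)²/(difference/SD)², 4.4/8.7 gives 62 per group and 0.4/0.8 gives 63. The t-based versions are 63 and 64, so 64 is reproduced. It is used below only as the number per arm. The article gives no SD or effect for DDS or ADDQoL, so the values below are assumptions.

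**What the reversed coefficient estimates.** Let the change score, given baseline, have mean μ in control, μ + δ in the treated arm, and normal residuals with variance σ² in both arms. With 1:1 allocation, Bayes' rule gives

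log odds(treated | change c) = [(c − μ)² − (c − μ − δ)²]/(2σ²) = (δ/σ²)c + terms free of c.

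The slope is therefore δ/σ². It equals the treatment effect δ only when σ² = 1.

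**Same effect, different residual SD.** 64 per arm, δ = -0.4, baseline in both models, 1,500 runs per row:

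| Residual SD | ANCOVA difference | δ/σ² | Median reversed slope | Odds ratio |
|---|---|---|---|---|
| 0.5 | -0.40 | -0.4/0.25 = -1.60 | -1.64 | 0.19 |
| 0.8 | -0.39 | -0.4/0.64 = -0.625 | -0.63 | 0.53 |
| 1.2 | -0.39 | -0.4/1.44 = -0.278 | -0.28 | 0.76 |

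The treatment effect is fixed, yet the odds ratio moves from 0.19 to 0.76.

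**Same effect and variance, different shape.** In a second simulation (4,000 runs per scenario, 64 per arm), δ = -0.5 × √0.75 = -0.433 and σ² = 0.75, so δ/σ² = -0.577. The mean reversed slope was -0.598 with normal, -0.691 with exponential and -1.133 with lognormal residuals. Multiplying back by 0.75 gives -0.45, -0.52 and -0.85, against a true -0.433. Converting the slope to points therefore fails most when residuals are clearly non-normal, which is when the fallback applies. Mean ANCOVA estimates were -0.43, -0.44 and -0.43.

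**Is the fallback needed, and is it a valid test?** Same second simulation, plus a scale from 1 to 6 with patients at the floor. Power is for an assumed effect of 0.5 residual SD (before flooring in the last row):

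| Outcome shape | Type I error, ANCOVA | Type I error, reversed | Power, ANCOVA | Power, reversed |
|---|---|---|---|---|
| Normal | 4.5% | 4.3% | 80% | 80% |
| Exponential | 5.1% | 4.7% | 80% | 79% |
| Lognormal | 4.5% | 3.5% | 82% | 80% |
| Floor-bounded | 5.3% | 5.1% | 76% | 76% |

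The Monte Carlo standard error at 5% is √(0.05 × 0.95/4000) = 0.34 percentage points. The two methods reached the same decision in 97% to 99.8% of runs. The reversed model is thus a usable test, slightly conservative in the lognormal case, and it has no power advantage.

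**Binary endpoints.** With two binary variables, the unadjusted odds ratio is identical in either direction. With a prognostic baseline covariate (64 per arm, assumed effects, 1,500 runs), the median odds ratio was 2.51 with response as outcome and 2.50 with arm as outcome.

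**The case against.** The strongest reply is that the inference is sound. The reversed model tests the right null hypothesis with about the right error rate and nearly the power of ANCOVA. It is reached only if normality fails twice, and group mean changes could be tabulated beside it. All of this stands. It lowers the severity and leaves the defect as one of estimation: raw means beside an odds ratio are not the baseline-adjusted difference with an interval that the first-choice analysis would give.

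Four stronger readings are tempting, and the documents do not support them.

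- *The fallback says nothing about treatment.* It does test for a difference; what is missing is an interpretable size.
- *The HbA1c proportions are spoiled too.* Read literally, section 2.6.4 points them to the reversed model, but the odds ratio is nearly the same either way. That section also allows departures according to the distribution of the variables.
- *The transformation step is impossible because change scores can be zero or negative.* The article names no transformation, and a cube root or a shifted logarithm is defined for such values.
- *Checking normality is itself an error.* The phrase can be read as referring to residuals, and the criterion may be set in an analysis plan that is not shown. The check is of little use here, but it is not wrong.

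**Conclusion.** The point holds for DDS, ADDQoL and the five continuous exploratory endpoints. If the last step is triggered, the planned result is an odds of allocation per score point, which moves with residual variance and distribution shape and cannot be turned into a treatment effect in points. For one assumed effect of -0.4 points it ranged from 0.19 to 0.76.

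This is a should-fix. The step is a contingency, its p-value is approximately valid, and neither the primary endpoint nor DTSQc is affected. The slope result δ/σ² rests on normal residuals with equal variance. The finding that ANCOVA suffices rests on 64 per arm and the shapes tried; more extreme distributions or far fewer completers were not examined.

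**What to change.** In section 2.6.3, remove the reversed logistic step for DDS and ADDQoL. Keep ANCOVA with the baseline score as covariate as the single analysis whatever the distribution, which also makes the transformation step unnecessary. Report the adjusted mean difference with a 95% CI from heteroscedasticity-robust (HC3) standard errors or a bootstrap. The simulations used ordinary standard errors, so this is an added safeguard. If a distribution-free check is wanted, add a rank-based ANCOVA or a proportional-odds model as sensitivity analysis, with the score as outcome and arm as predictor. Apply the same wording to the continuous endpoints in section 2.6.4.

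For the three HbA1c proportions, state that logistic regression has response as outcome, with arm and baseline HbA1c as predictors. This is clarification only.

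The cost is analysis wording and code. No data collection, sample size or primary analysis changes.

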#### Clinical visits

2.4.1

After inclusion and randomization, individuals in both treatment and control groups met with a diabetes nurse at 13, 26, and 52 weeks. A physician was also present for the inclusion visit and the 52-week follow-up where physical examinations were performed. At each follow-up visit HbA1c, blood pressure, and weight were measured. Insulin type and doses, type of glucose monitoring, and insulin delivery method were also checked, as well as the occurrence of adverse events. At randomization and at 26 and 52 weeks, diabetes distress was measured using the Diabetes Distress Scale (DDS) (17), which summarizes overall level of diabetes distress, as well as the level in specific areas. Quality of life was measured using the Audit of Diabetes Dependent Quality of Life (ADDQoL) (18), which measures present quality of life, the impact of diabetes on quality of life, and the average weighted impact of 19 different areas in life and how they are affected by diabetes. Hypoglycemia confidence was measured using the Hypoglycemia Confidence Scale (HCS) (19) which is a 9-item self-report scale which evaluates confidence in preventing and addressing hypoglycemic events, and treatment satisfaction was measured using the Diabetes Treatment Satisfaction Questionnaire status and change version (DTSQs and DTSQc) (20, 21), containing eight items scored on 7-point scales that are summed to a total treatment satisfaction score.

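### The secondary endpoint DTSQc has no named ANCOVA covariate and an unadjusted Mann-Whitney fallback, although baseline DTSQs is collected and could be used in both

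*Protocol article*

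**What the plan says.** Section 2.4.1 (Clinical visits) lists both forms of the satisfaction questionnaire, the "Diabetes Treatment Satisfaction Questionnaire status and change version (DTSQs and DTSQc"). Table 3 in section 2.5 makes "DTSQc (Diabetes Treatment Satisfaction Questionnaire) score at week 52" a secondary endpoint. It is the only secondary endpoint not worded as a change from baseline. The same table lists "Changes in DTSQs score from baseline to week 52" as exploratory, so a baseline DTSQs value must exist.

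Section 2.6.3 gives the analysis: "DTSQc score at week 52 between the two treatment groups will be analyzed using ANCOVA in case the assumption of normal distribution is met". The alternative for data that fail this condition is worded "or otherwise by using the Mann-Whitney U-test". For diabetes distress, the same section specifies a model "using ANCOVA with DDS score at baseline as the covariate". If normality fails even after transformation, it moves to a logistic regression with "change in DDS as main effect variable, and DDS score at baseline as the covariate". Quality of life follows the distress method. Section 2.6.2 names baseline HbA1c as the covariate for the primary analysis, and section 2.6.4 adjusts every exploratory endpoint for its baseline value.

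**The concern.** DTSQc is the one confirmatory outcome for which the article names no covariate, and the one whose written fallback drops adjustment altogether. The ranking is also uneven: the exploratory DTSQs change is to be adjusted for baseline, while the secondary DTSQc has no adjustment stated.

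Baseline DTSQs is the obvious candidate. It is the status form of the same questionnaire, measured before treatment, and a patient's starting satisfaction may plausibly relate to the change reported a year later. If it does, leaving it out gives a wider confidence interval and lower power on a named secondary endpoint than the collected data allow.

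**Working it through.** **1. The plan's own figure.** The article gives no SD, effect or power for DTSQc. Its only sample-size calculation (section 2.6.1) is for HbA1c: a difference of 4.4 mmol/mol (0.4 percentage units), SD 8.7 (0.8), 80% power, alpha 0.05, 64 per group, 142 in total.

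- Normal approximation, n = 2(1.96 + 0.84)² × (SD/difference)²: 62 per group from 4.4 and 8.7, or 63 from 0.4 and 0.8.
- Two-sample t-test: 62.3, so 63, or 63.8, so 64.
- Dropout: 128/0.9 = 142.2.

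The stated figures reproduce, and the present point does not alter them. Below, 64 per group is borrowed only as a convenient number of completers.

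**2. The three secondary analyses side by side (section 2.6.3).**

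| Endpoint | Main model | Covariate named | Fallback | Baseline kept in fallback |
|---|---|---|---|---|
| DDS change | ANCOVA | baseline DDS | transformation, then logistic regression | yes |
| Quality-of-life change | as DDS | by the DDS method | as DDS | yes |
| DTSQc at week 52 | ANCOVA | none | Mann-Whitney | no |

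**3. What an ANCOVA with only a group term would be.** It is the two-sample t-test. A check on simulated data with 64 per group gave the same p-value from both, 0.8308. The model is therefore not fully defined until a covariate is named.

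**4. Gain in standard error.** Let r be the within-arm correlation between baseline DTSQs and week-52 DTSQc. The documents give no value, so r is assumed. Ignoring the one degree of freedom spent on the covariate, the ratio of adjusted to unadjusted standard error is √(1 − r²), and the equivalent unadjusted sample size is 128/(1 − r²).

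- |r| = 0.2: √0.96 = 0.980, a 2% reduction; 128/0.96 = 133.3, about 5 extra patients.
- |r| = 0.4: √0.84 = 0.917, an 8% reduction; 128/0.84 = 152.4, about 24 extra.
- |r| = 0.5: √0.75 = 0.866, a 13% reduction; 128/0.75 = 170.7, about 43 extra.

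**5. The same in power.** The standardised effects of 0.5 and 0.4 are illustrative assumptions. Power = Φ(d√(64/2)/√(1 − r²) − 1.96). For d = 0.5 and r = 0, d√32 = 2.828, and Φ(0.868) = 80.7%. For the Mann-Whitney test with normal data, 64 is multiplied by its efficiency 3/π.

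| Analysis | d = 0.5 | d = 0.4 |
|---|---|---|
| Mann-Whitney, normal data | 78.9% | 59.9% |
| Unadjusted means | 80.7% | 61.9% |
| Adjusted, \|r\| = 0.2 | 82.3% | 63.7% |
| Adjusted, \|r\| = 0.4 | 87.0% | 69.5% |
| Adjusted, \|r\| = 0.5 | 90.4% | 74.3% |

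At d = 0.5, adjustment over the assumed range adds about 2 to 10 percentage points compared with unadjusted means.

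**The case against.** The best reply is that an unnamed covariate is not an absent one. The article says ANCOVA, which implies a covariate. It is a condensed account, and a statistical analysis plan that is not shown may name one. That stands. A reader might infer that the planned DTSQc analysis is simply a t-test, but the text does not say so, and the missing name alone would not be worth raising. What the reply does not reach is the fallback: the Mann-Whitney test is a choice written on the page, and it carries no covariate.

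A second reply is that the fallback is legitimate. This also stands. In a 1:1 randomised comparison it controls type I error, and its own loss against unadjusted means with normal data is only about 2 points of power. A reader might infer bias from chance imbalance in baseline satisfaction, but any unadjusted randomised comparison is exposed to such imbalance without being invalid.

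Third, the normality rule might be read as post hoc. It is not: the check and the switch are both laid down in section 2.6.3. The choice depends on the data, but it is pre-specified. Nor is the loss of a mean difference peculiar to DTSQc, since the logistic fallback for DDS, with group as the dependent variable, gives none either.

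Fourth, a baseline-adjusted satisfaction analysis is already planned for DTSQs. That is true, but it is exploratory and does not replace the secondary endpoint.

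Finally, a reader might infer that DTSQc was never administered at baseline. Table 3 suggests it, but section 2.4.1 states the questionnaire visits explicitly only for the DDS ("At randomization and at 26 and 52 weeks, diabetes distress was measured using the Diabetes Distress Scale (DDS")) and does not separate the two DTSQ forms. The point does not need that inference. It needs only that baseline DTSQs exists.

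**Conclusion.** The point holds as a minor one. For DTSQc at week 52, the article leaves the ANCOVA covariate unnamed and fixes an unadjusted fallback, out of line with its treatment of diabetes distress and quality of life, while a usable baseline covariate is in the dataset. The consequence is lost precision, with no bias and no inflation of type I error.

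The size rests wholly on an assumed correlation. With |r| from 0.2 to 0.5 the standard error would fall by about 2% to 13%. At the low end the gain is negligible, and if r is near zero there is none. It is a free improvement to one of three secondary endpoints, with no effect on the primary analysis or the sample size.

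**What to change.** In section 2.6.3, or in the statistical analysis plan if it is still open, state before outcomes are compared by group that:

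- DTSQc at week 52 is analysed by ANCOVA with treatment group and baseline DTSQs total as covariate.
- If the normality assumption fails, the fallback is also baseline-adjusted, for example a rank ANCOVA on baseline DTSQs, in place of the unadjusted Mann-Whitney test.

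If the analysis plan already names baseline DTSQs for the ANCOVA, only the fallback needs changing.

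The cost is one or two sentences and slightly more analysis work, with no new data. The one drawback is dependence on complete baseline DTSQs, so the text should also say how participants without it are handled.

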#### Exploratory analyses

2.6.4

Exploratory endpoints will be analyzed in the same way as the primary and secondary endpoints, using ANCOVA for normally distributed variables, ANCOVA on transformed variables in case the assumption of normal distribution is not met, or logistic regression as described above. All exploratory endpoints will be adjusted for baseline values. Possible differences may exist depending on the distribution of variables.

An exploratory analysis is planned describing the psychological methods used by psychologists in the study and an analyses with respect to if results differed by psychologist, i.e. if an interaction exist between psychologist and treatment effect. We will also analyze if treatment effects relate to the number of consultations with psychologist.

## Discussion

3

This paper describes the protocol of a randomized controlled trial investigating whether treatment with a diabetes-educated psychologist can help patients with type 1 diabetes improve glycemic management. Although HbA1c is the primary endpoint, an important objective is to investigate whether psychological treatment can help decrease diabetes distress, as many people with diabetes also struggle with this aspect of the disease.

Psychosocial factors such as depression, lack of motivation, and diabetes distress are recognized as important aspects that affect glucose management. However, psychologists are generally not involved in diabetes care teams to the same extent as other professionals such as nurses or dietitians. Previous studies have sought to investigate the effect of different psychological interventions on HbA1c. Interventions have varied from CBT-based treatments to motivational approaches and counselling. Some studies have found a significant improvement while other results have been mixed or shown no significant improvement (3, 10, 11).

Previous studies have assessed psychological interventions in both group and individual formats (3, 10, 11). Both treatment approaches have potential positive and negative aspects. Interventions given in a group setting can provide a sense of community and decrease feelings of loneliness or isolation. While individual treatment lacks the aspect of having input from other people in similar situations, it can more easily be focused on the specific problem areas of the patient. Additionally, some patients may not be comfortable attending group treatment for various reasons, including not wanting to discuss sensitive or emotional topics with others. Considering these aspects, an individual treatment approach was chosen for this study.

An important aspect of the present study was the diabetes education that psychologists received before treating patients. Education included basic information about diabetes, as well as specific psychosocial issues that many patients struggle with. It has been suggested that specific knowledge about the challenges of living with diabetes is important for psychologists to be able to identify problem areas and provide relevant treatment (9).

An aspect that can be seen as a limitation to this study is that psychological treatment is not strictly manual based, which could make replication difficult in future research, since treatment might not look the same for every participant. However, a number of guidelines were followed to secure quality and replicability of the intervention. For example, all patients were screened for depression before starting treatment. Psychologists also received a list of common psychosocial barriers for glycemic management that were reviewed with each patient at the beginning of treatment (**Table 2**) to identify focus areas. All psychologists were educated in CBT, which was the first choice of treatment before considering other methods. To make the intervention more representative of a real-life scenario, 10 different psychologists provided treatment. Within the framework of these guidelines, it was also important to allow for the treatment to be flexible and to be tailored to the needs of the individual patient.

In summary, this study seeks to investigate whether a diabetes-educated psychologist can help patients lower HbA1c levels and decrease diabetes distress. Should this study show beneficial results, it could provide justification for psychologists to become more involved in diabetes care going forward. On the other hand, improvements in diabetes distress or other psychosocial factors without significant effects on glucose levels will also be essential for patients in clinical practice. Either way, we hope this study will increase knowledge about how to help patients who struggle managing diabetes either physically or emotionally.

